#### ANI_a_ <ANI :_min_

In this area, we consider that analgesia is insufficient. This event is treated by increasing the infusion pump rate.

**If(**InF<InFmax)**and**(S_a_ <SaT) **then** InF = InF+InI (4)

#### ANI_min_ <ANIa< ANI_max_ :

In this area, we consider that analgesia in adequate. However, in order to anticipate, we consider the ANI_a_ slope (S_a_ ) changes in order to regulate the infusion rate.

**If**(ANI_a_ <ANI_mean_ **)and**(S_a_ <-S_a_ T)**and**(InF+InI<InF )_max_

**then** InF = InF+ InI (5)

**If**(ANI_a_ > ANI_mean_ **)and** (S_a_ >S_a_ T)**and**(InF- InI>InF )_min_

#### ANIa>75 :

**then** InF = InF- InI (6)

In certain condition, we consider that if ANI is too high, ANS doesn't respond to noxious stimuli. This effect could be explained by an opioid overdose which would require an infusion flow decrease.

**If**(S_a_ >0)**and**(InF- InI>InF_min_ **)then** InF = InF- InI (7) Each infusion rate change is followed by a RefP refractory period.

In order to avoid arterial hypotension (SBP<80 mmHg), we added two rules on systolic blood pressure (SBP).

**If** SBP<90 **then** InF = InFmin (8)

**If** SBP<80 **then** InF = 0 (9)

In the case of SBP<80 mmHg, the regulation algorithm is shut down until SBP recovers a value over 85 mmHg. Rules (8) and (9) have the highest level of priority.

*C - Algorithm implementation*

From a technical point of view, the system consists in a software ("controller") implemented on a classical personal computer allowing to adapt in real time the syringe pump infusion rate according to ANI_i_ and ANI_a_ evolutions. ANI_i_ and ANI_a_ values are obtained from the Physiodoloris monitor communication interface and SBP is obtained from the Anesthesia monitor (Datex Ohmeda AS-5, GE Healthcare or

Intelliview® Philips^TM^ ). The syringe pump (Alaris GH, Cardinal health) and the two monitors are linked to the computer through a Keyspan® 4-port serial to USB adapter.

The software also allows users to enter patient characteristics (age, size, weight, ASA) and constants values used for regulation. Thanks to the interactive aspect of the controller, all the predefined constants can be adapted and manually changed during the regulation. Finally, a specific software interface allows users to follow the variable's evolution, the syringe pump status and the regulation results. Direct syringe pump commands are also available in order to allow the anesthesiologists to manually adapt the syringe pump infusion flow or to shut down the automatic regulation.

Constants used for regulation are defined as follow:

- ***ANI =75_max_***
- ***ANI =50_min_***
- ***S T=7_a_***
- ***S T=25_i_***
- ***InI=0.01 µg/kg/min***
- ***InF_min_ =0.05 µg/kg/min***
- ***Inf_max_ =0.6 µg/kg/min***
- ***BolusI= 0.04 µg/kg/min***
- ***RefP=10 s***

Blood pressure is measured every 2.5 minutes.

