##### Secondary objectives and hypotheses

To determine whether the automated administration of remifentanil by the ANI-loop device allows:

- improving hemodynamic stability during propofol general anesthesia.
- increasing the time spent with an ANI between 50 and 70.
- reducing immediate post-operative pain.

In the *"ANI-loop*" arm only: determine whether ANI-loop enables fully automated administration (i.e. without the need to disengage the device).

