##### Evaluation criteria

- - 1. Definitions
- *baseline" values* for heart rate (HRbl) and systolic blood pressure (SBPbl) are the mean of 3 measurements taken before the start of anesthesia
- *hemodynamic reactivity*: HR > 120% of HRbl or SBP > 120% of SBPbl
- *hypotension*: PAS <75 mmHg
- *bradycardia*: HR < 40 min-1
- *intervention*: begins with skin preparation, includes surgery and ends with the end of dressing
  - 1. main criterion, making it possible to meet the main objective

Total quantity of remi administered (value related to weight and duration of intervention).

- - 1. secondary criteria to meet secondary objectives:

NB: several criteria are assessed after the patient wakes up, between extubation (H0) and H2 120 min after extubation. The patient does not need to be in the intensive care unit for this assessment; he/she can be in his/her hospital room.

- Proportion of time spent in hemodynamic reactivity, hypotension or bradycardia during the procedure. This proportion will be equal to the cumulative duration of each episode of reactivity, hypotension or bradycardia, divided by the duration of the procedure Total dose of Ephedrine.
- ANIi and ANIm: proportion of time spent during the intervention in the following intervals :

<50, [50-70], >70

- hypnotic component measurement index (BIS® or Entropie®): proportion of time spent during the procedure in the following intervals: <40, [40-60], >60
- ANI, heart rate, blood pressure, FetCO2, Pmax (ventilator) 5 min before start of procedure, 5 min after start of procedure and 20 min after start of procedure.
- Pain assessed by visual analog scale (VAS) between H0 and H2, every 15 min.
- Total quantity of morphine administered between end of surgery and H2 post-op.
- Total quantity of ketamine administered between end of surgery and H2 post-op.
- Frequency of postoperative nausea/vomiting assessed at H2.
- Number of changes in remifentanil flow rate during the procedure.
- Total quantity of propofol administered (absolute value, value related to weight, value related to weight and duration of procedure).
- Number of propofol target changes during the procedure.

In the *"ANI-loop"* arm only: number and total duration of disengagements of the ANI-loop device during the operation, i.e. the number of times and cumulative duration that the closed-loop system had to be interrupted and replaced by manual control, as in the standard practical arm.

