- propofol target adapted in both arms to maintain the hypnotic component index (BIS® or Entropy®) in the range [40-60]. During *the procedure*, propofol target changes will be made 1 minute after the last target change has become effective, and will follow the indications in table 1. This corresponds to the usual management in the burn unit of the Burn Treatment Center.

|  |  |  |
| --- | --- | --- |
| component  hypnotic | propofol target |  |
| >80 | + 2.0 |  |
| >60 | + 1.0 |  |
| <40 | - 0.5 |  |
| <25 | - 1.0 |  |
| **Table 1: Adaptation of propofol targets in both arms** | | |

|  |  |  |
| --- | --- | --- |
| ANI | target remi |  |
| <35 | + 2.0 |  |
| <50 | + 1.0 |  |
| >70 | - 0.5 |  |
| >90 | - 1.0 |  |
| **Table 2: Adaptation of remi targets in the "standard practice" arm** | | |

- remifentanil target
  - **in the *standard practice* arm**: increased to 4 ng.ml-1 at the start of *the procedure*, then adjusted to maintain ANI in the range [50-70] as indicated in Table 2. Target changes are made 1 minute after the last target change has become effective. This corresponds to usual management at the Burn Treatment Center.
  - **in the *ANI-loop* arm**, the automatic mode of the ANI-loop device is engaged at the start of *the procedure*. The flow of remifentanil is automatically regulated by the ANI-loop. The anaesthetist can switch to manual mode at any time in the event of inadequate regulation (device disengagement). The device is switched off at the end of the *procedure.*

Pre-emptive analgesia

- local infiltration of skin sample area with naropein 2 mg.ml-1 during

*intervention*

- paracetamol 1g IVL at end of *procedure*
- sufentanil 0.12 µg.kg-1 (max 10 µg) IVL at *end of procedure*

Prevention of postoperative nausea/vomiting

- ondansetron 4 mg IVL

Postoperative analgesia

- morphine titration according to Visual Analogue Scale (VAS), bolus of 3mg every 3 min (max 12mg)
- ketamine 20 mg IVL for persistent pain with VAS ≥ 40

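### Full automation is judged by disengagements alone, although constants can be changed by hand while the loop runs, so autonomy can be overstated; the flow-change count does not close the gap

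*Protocol*

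**What the plan says.** **Objective.** Section 3.2 (Secondary objectives and hypotheses) sets, for the ANI-loop arm only, the aim to "determine whether ANI-loop enables fully automated administration (i.e. without the need to disengage the device".

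**Endpoint.** Section 4.3 (Evaluation criteria) measures this by the "number and total duration of disengagements of the ANI-loop device during the operation". It explains these as the times, and total duration, that "the closed-loop system had to be interrupted and replaced by manual control, as in the standard practical arm". The anaesthesia procedure in section 5.2 uses the word in the same way: "The anaesthetist can switch to manual mode at any time in the event of inadequate regulation (device disengagement".

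**What the user may do.** Appendix I, part B, lists nine regulation constants as set by the user: the upper and lower ANI limits, two slope thresholds, the flow increment, the minimum and maximum flow, the bolus increment and the refractory period. Part C gives a value for each and also states: "Thanks to the interactive aspect of the controller, all the predefined constants can be adapted and manually changed during the regulation". On the pump itself it says: "Direct syringe pump commands are also available in order to allow the anesthesiologists to manually adapt the syringe pump infusion flow". The other use that it names for these commands is stopping the loop altogether.

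**Related criterion.** Section 4.3 also lists the "Number of changes in remifentanil flow rate during the procedure". Under section 4.5 (Analysis method and strategy), quantitative secondary endpoints are compared between arms by a t-test or a Mann-Whitney test. Criteria that exist only in the ANI-loop arm are described without a test.

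**The concern.** The objective is about automation, but the endpoint records only one form of human intervention. An anaesthetist who moves an ANI limit, a flow limit or the increment while the loop is running alters what the device delivers. The loop is neither interrupted nor replaced, so the endpoint scores zero and the procedure counts as fully automated.

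At stake is the answer to a stated objective, with any error in the device's favour. One might expect the flow-change criterion to reveal the hidden interventions. It does not separate human from automatic changes, and it does not count the same thing in the two arms.

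**Working it through.** **Step 1. Which human actions reach the endpoint?**

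| Action in the ANI-loop arm | Permitted by | Loop interrupted and replaced? | Counted? |
|---|---|---|---|
| Switch to manual mode | Section 5.2 | Yes | Yes |
| Shutdown of the regulation | Appendix I, part C | Yes | Yes |
| Manual flow command | Appendix I, part C, as an alternative to shutdown | Not stated | Unclear |
| Change of a constant during regulation | Appendix I, part C | No | No |

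The protocol does not say that the listed values are locked for the trial. It does not ask that changes to them, or manual flow commands, be recorded.

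**Step 2. Direction and possible size.** The protocol gives no frequency for such actions, so this is an illustration on assumed rates. Let d be the share of ANI-loop patients with a counted disengagement, and q the share of the remaining patients with an uncounted manual action.

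- Apparent autonomy = 1 − d
- Actual autonomy = (1 − d)(1 − q)
- Overstatement = (1 − d)q, which is never negative

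With 26 patients in the arm (section 4.4):

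| d | q | Apparent (patients) | Actual (patients) | Overstatement |
|---|---|---|---|---|
| 0 | 0 | 26 | 26 | 0 points |
| 0 | 10% | 26 | 26 × 0.9 = 23.4 | 10 points |
| 0 | 30% | 26 | 26 × 0.7 = 18.2 | 30 points |
| 20% | 30% | 26 × 0.8 = 20.8 | 20.8 × 0.7 = 14.6 | 0.8 × 0.3 = 24 points |

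**Step 3. Does the flow-change count fill the gap?** In the ANI-loop arm the algorithm sets the flow itself (Appendix I, rules 4 to 9), so the count is mainly of algorithm steps. In the control arm the anaesthetist sets a concentration target on a pump driven by a pharmacokinetic model (section 5.2), and the pump turns that target into a flow. The protocol does not say whether the control count means pump flow variations or target changes. For propofol, section 4.3 counts target changes, so the protocol knows the difference. Neither reading gives human actions in both arms.

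The ceilings do not settle the direction of the difference. With a 10 s refractory period the device could change flow at most 60/10 = 6 times a minute, or 6 × 60 = 360 an hour. A control target may change 1 minute after the previous one has taken effect, so fewer than about 60 times an hour. These are upper limits in different units. Rules 4 to 7 also require conditions on ANI, slope and flow limits. With averaged ANI between 50 and 75 and a slope within ±7, none of those rules changes the infusion rate. The whole flow range is (0.6 − 0.05)/0.01 = 55 steps, or 550 s (about 9 minutes) at one step per 10 s. Sustaining 360 changes an hour would need repeated reversals.

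**Step 4. Effect on the primary analysis.** The planned difference is 0.30 − 0.24 = 0.06 with SD 0.075, a standardised difference of 0.06/0.075 = 0.8. At two-sided 5% and 80% power, the t-test calculation gives 25.52, hence 26 per group (power 0.807). The stated 26 per group is reproduced and nothing in this point changes it.

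**The case against.** The strongest reply is that Appendix I describes what the software can do, whereas section 5.2 describes what the trial does: automatic mode is engaged at the start, and the only manual option named is the switch to manual mode. Nobody is told to retune constants, and one set of values is listed. This stands against a reader who infers that autonomy **will** be overstated. The documents support only that it can be.

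Further replies, and what remains of them:

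- **Objective and endpoint agree, since the objective itself defines full automation as no need to disengage.** They agree in wording. The definition still lets a procedure steered through its constants pass as fully automated.
- **Protocol deviations must be reported with their reason (Quality control and assurance).** Because Appendix I expressly allows the constants to be changed, such a change is not clearly a deviation.
- **The case report form and the statistical analysis plan may deal with it.** Neither is shown, so it cannot be said that these actions will go unrecorded. But the endpoint is fixed in the protocol, and the analysis plan need only be validated before database freeze, when data never collected may be unrecoverable.
- **A manual flow command is naturally manual control, hence a disengagement.** That is a reasonable reading. Its listing beside shutdown as an alternative leaves it ambiguous, so one should not say that it is plainly uncounted.
- **The flow-change criterion is never offered as a measure of autonomy.** True. It is nevertheless due for a between-arm test of two unlike quantities.

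Two other inferences are tempting and fail. The first is that a several-fold difference in flow changes is guaranteed. The 360 and 60 are ceilings in different units, and if the control pump's own flow variations count, even the direction is unknown. The second is that the primary result could not be attributed to the algorithm with its listed constants. The main objective (section 3.1) and the design (section 4.1) concern the device under an anaesthetist's supervision, and an adjustable controller is part of that device.

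**Conclusion.** The point holds in a limited form. Disengagement is the only measure of full automation. A constant changed while the loop runs escapes it, and a manual flow command may or may not be caught. Any error favours the device. Its size is unknown, and it is zero if no such action occurs; the 10 and 30 point figures rest on assumed rates. Separately, the number of remifentanil flow changes is not a like-for-like comparison between arms and does not show human intervention in either.

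The scope is modest: one descriptive, single-arm secondary objective and one between-arm secondary criterion. It still merits correction before enrolment, because the bias runs one way and the remedy is cheap.

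**What to change.** 1. State in the protocol whether the regulation constants stay at the values listed in Appendix I, part C, during the procedure. This review takes no position on which values or rule to use.
2. If they may change, record every change of a constant made while the loop runs and every direct flow command, from the controller log if it can be exported or in an eCRF field. State which of these count as a disengagement.
3. Beside the number and duration of disengagements, report the proportion of ANI-loop procedures with no human remifentanil action of any kind.
4. For the between-arm comparison, use human-initiated remifentanil actions: target changes in the control arm; disengagements, constant changes and manual flow commands in the ANI-loop arm. Present raw flow changes descriptively only.

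The cost is one definition and one log export or eCRF field. The autonomy figure may look less favourable.

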#### APPENDIX II: State of the art in loop delivery systems for intravenous anesthetics

The CE-marked PhysioDoloris monitor (MDoloris Medical Systems, Loos, France), on the market since 2010, is a recognized measure of the state of the autonomic nervous system, enabling real-time assessment of parasympathetic tone (paraS) based on non-invasive electrocardiogram collection. It continuously displays the Analgesia Nociception Index (ANI), corresponding to the relative amount of paraS tone, which varies between 0 and 100. Several studies have demonstrated that ANI provides a measure of the state of the antinociception/nociception balance during general anesthesia^8,9,11-14^ . In the conscious patient in the post-interventional monitoring room, after general anaesthesia, ANI enables pain levels to be measured^15^ , except after prolonged sevoflurane anaesthesia^16^ . Outside the perioperative period, in the conscious patient, ANI shows a significant relationship with pain levels, in both children^17^ and adults .^18^

#### It is important to note that the proposed study does not concern the PhysioDoloris monitor. The study focuses on an innovative medical device (see appendix II) which enables the automated administration of remifentanil based on elements from the usual hemodynamic monitoring (heart rate and blood pressure) combined with the continuous measurement provided by the PhysioDoloris monitor (ANI).

Automated administration of propofol for induction and maintenance of general anesthesia (GA) is a technique used by many teams today. The target signal to be maintained within a predefined interval is derived from the electroencephalogram (EEG) in the vast majority of cases: it is the BiSpectral® index (Aspect Medical Systems, MA) and EEG entropy (GE HealthCare). Two medical devices, EasyTIVA® (MedSteer, Suresnes, France) and McSleepy® (McGill University, Quebec, Canada), are currently in the CE marking phase, having completed pre-industrial proof of concept^19,20^ . A third medical device for closed-loop administration of total intravenous general anesthesia (TIVA) has been CE-marked and marketed since 2016, the Concert-CL® (Veryark® Technology Co., Ltd., Guangxi, China) .^21,22^

The analgesic component of GA has seen significant progress over the last decade, with the commercialization of several autonomic nervous system (ANS) monitors that have been used to measure the anti-nociception/nociception balance during GA^23-31^ . The absence of a specific physiological signal for nociception is the main technical difficulty in developing a feedback loop for the administration of morphine analgesia. Some authors have demonstrated that mean arterial pressure can be used as a target for closed-loop administration of alfentanil^32^ , while others have developed a specific score, the analgoscore, which combines variations in heart rate and arterial pressure (McSleepy® system)^19,20^ . Finally, other authors use EEG and cortical arousal induced by nociceptive phenomena to distinguish between the patient's need for hypnotics and morphine (EasyTIVA® system): this device has already been extensively evaluated in a variety of clinical settings^33,34^ , and has demonstrated a real advantage in assessing the morphine-sparing effects of dexmedetomidine use^35^ or the morphine needs of special populations such as morbidly obese patients^36^ . Two recent meta-analyses highlight the safe use of closed-loop delivery devices, and in some cases their superiority to manual delivery systems .^37,38^

